### DNA isolation

DNA extraction of the vaginal swabs and urine samples will be performed with the Chemagen machine (Chemagen, Baesweiler, Germany) using the buccal swab extraction kit according to the manufacturer’s instructions. First, collected swabs and urine samples will be thawed and vortexed. 200 μl of sample will be incubated with 200 μl of Chemagen lysisbuffer and 10 μl Proteinase K (Qiagen, Hilden, Germany) at 56 °C while shaking at 500 rpm. DNA will be extracted using the protocol buccal Swab Prefilling. Finally, DNA will be eluted in 100 μl of Chemagen Elution buffer.

### Sequencing of the 16S ribosomal RNA

Picogreen dsDNA assay (Thermofisher, MA, USA) will be used for sample DNA concentration measurement. For sequencing, the V3-V4 region of the 16S rRNA gene region will be amplified using the individually distinguishable dual index primer sets. The rDNA amplification primers will be the universal primer set 319F/806R and they will be altered to also encode the Illumina sequencing primer and barcode labelling sequences. PCR will include 30 s at 98 °C, 30 cycles of 10 s at 98 °C, 15 s at 58 °C, and 15 s at 72 °C and three minutes at 72 °C. The AMPure XP magnetic bead assay (BeckmanCoulter Genomics, Danvers, MA, USA) will be used for purification of the amplified DNA. The following formula will be used for recalculation into nM and equalized to 12 nM:$$ \left[\mathrm{nM}\ \mathrm{DNA}\right]=\frac{\left(\mathrm{DNA}\ \mathrm{concentration}\ \left(\frac{\mathrm{ng}}{\upmu \mathrm{l}}\right)x\ 1e6\ \left(\frac{\upmu \mathrm{l}}{\mathrm{L}}\right)\right)}{\Big(\mathrm{sample}\ \mathrm{fragment}\ \mathrm{size}\ \mathrm{in}\ \mathrm{bp}\ x\ \mathrm{656,4}\ \left(\mathrm{g}/\mathrm{mole}\right)} $$

If DNA concentrations fell below 12 nM, pooled DNA will be concentrated by vacuum evaporation.

### Next generation sequencing

NGS will be performed using a Miseq tabletop sequencer (Illumina, San Diego, CA, USA) by the Tumor Genome Analysis Core group of the Department of Pathology at the VU University Medical Centre in Amsterdam, The Netherlands. QIIME will be utilized to remove primer and index sequences, while paired end reads with a minimum overlap of six nucleotides and a minimum combined length of 400 nucleotides are assembled to produce identifiable sequences. The Usearch method will be utilized to produce operational taxonomic units (OTU) clusters. During this process, the sequences will be sorted on length and abundance of identical reads, will be checked for chimeric sequences and the sequence similarity threshold is set to 0.97 to denoise the data. The database described by Srinivasan et al. [21] will be used to assign sequences on a genus to species level by using the PyNAST method for sequence alignment and subsequently assignment using the RDP classifier method. The remaining sequences will be BLASTed, and will be included if the sequence can be identified at a genus or species level.

### Interspace profiling

Amplification of the intergenic spaces (IS) regions will be performed with the IS-pro assay, according to the protocol provided by the manufacturer (IS-Diagnostics, Amsterdam, the Netherlands). IS-pro is a eubacterial technique based on the detection and categorisation of the length of the 16S–23S rRNA gene IS region. The length of this IS region is specific for each bacterial species. Phylum-specific fluorescently labelled PCR primers will be used for taxonomic classification [22].

Briefly, the procedure consists of two separate standard PCRs: the first PCR mixture contains two different fluorescently labelled forward primers targeting different bacterial groups and three reverse primers providing universal coverage for those groups. The first forward primer is specific for the phyla *Firmicutes, Actinobacteria, Fusobacteria*, and *Verrucomicrobia* (FAFV), and the second labelled forward primer is specific for the phylum *Bacteroidetes*. A separate PCR mixture includes a labelled forward primer combined with seven reverse primers and is specific for the phylum *Proteobacteria*.

A GeneAmp 9700 PCR system (Applied Biosystems, Foster City, CA) will be used to perform the amplifications. After PCR, 5 μl of PCR product will be mixed with 20 μl of formamide and 0.2 μl of custom size marker (IS-Diagnostics, Amsterdam, The Netherlands). DNA fragment analysis will be performed on an ABI Prism 3500 genetic analyser (Applied Biosystems, Foster City, CA, USA). Data will be analysed with the IS-pro proprietary software suite (IS-Diagnostics, Amsterdam, The Netherlands), and the results will be presented as bacterial profiles. Automated species identification of IS-pro peaks will be done with the dedicated IS-pro software suite (IS-Diagnostics, Amsterdam, The Netherlands), in which peaks are linked to a database containing IS-profile information of > 500 microbial species. Peaks of < 500 relative fluorescence units (RFU) will be regarded as background noise and will be discarded from further analysis [22, 23].

### Microbiome analysis and algorithm building

The vaginal microbiome profile of each participant will be assigned to one of five community state types (CST) based on the dominant microbial species, as described by Ravel et al.^10^ Microbial communities in group I are dominated by *L. crispatus,* whereas group II, III, and V are dominated by respectively *L. gasseri, L. iners,* and *L. jensenii.* Group IV contains a heterogeneous group including species such as *Prevotella*, *Dialister*, *Atopobium*, *Gardnerella*, *Megasphaera*, *Peptoniphilus*, *Sneathia*, *Eggerthella*, *Aerococcus*, *Finegoldia*, and *Mobiluncus.*

The prediction model will be composed by analysis of the microbiological data will be performed in Spotfire 7.6 (TIBCO Spotfire Inc., Somerville, MA, USA). First, a distance matrix will be created on cosine distances of all possible sample pairs. Cosine distances are calculated with the following formula:

$$ \mathrm{dissimilarity}=1-\mathit{\cos}\left(\theta \right)=1-\frac{\sum_{i=1}^n{A}_i\times {B}_i}{\sqrt{\sum_{i=1}^n{\left({A}_i\right)}^2\times}\sqrt{\sum_{i=1}^n{\left({B}_i\right)}^2}} $$

The resulting data will be clustered with the unweighted pair-group method with arithmetic mean (UPGMA)4 and plotted as a heatmap.

To answer the questions of this study, an algorithm will be built based on the composition of the vaginal microbiome profile. First, the algorithm will be built by exploration of the pregnancy outcomes per CST. In a subsequent step, the data will be analysed for species content and microbial diversity per phylum. The formula will be validated for prediction of failure to become pregnant after (the first) fresh embryo transfer during the IVF or an IVF-ICSI treatment. Sensitivity will be calculated as true positive (TP) / (TP + false negative (FN)) and specificity as true negative (TN) / (TN + false positive (FP)). Predictive accuracy will be determined as the correlation between the predicted outcome and the actual outcome.

The vaginal samples that meet the prediction model for failure to become pregnant will be defined as ‘unfavourable microbiome profiles’. The vaginal samples that will not comply with the prediction model for failure to become pregnant will be defined as a ‘favourable microbiome profile’. Additionally, we will explore whether we can stratify these samples with a favourable microbiome profile into an average and a high chance to become pregnant based on additional bacterial species.

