## Background

Assisted Reproductive Technologies (ART) such as in-vitro Fertilization (IVF) [1] with or without Intra Cytoplasmic Sperm Injection (ICSI) [2] are used to assist the 10–15% of couples affected by subfertility [3]. At present the pregnancy rate is around 25% for the first attempt (cycle) and cumulative ongoing pregnancy rates after additional cycles vary between 40 and 50% depending on the number of treatment cycles [4, 5]. Because of the psychosocial, physical and financial burden of ART, prediction of accurate outcome is needed. Current prediction models perform moderately well and are based upon pure clinical parameters such as age, number of previous failed IVF treatments, and the cause of subfertility [6].

However, at the department of Urology and the division of Reproductive Endocrinology and Infertility of the department of Obstetrics & Gynaecology both in the Erasmus University Medical Centre, a new predictive algorithm for the outcome of IVF or IVF-ICSI based on the microbial composition (population of different bacteria in a given sample) has been developed. The collection of microorganisms that live on or in the human body is known as our microbiota and its complete genetic profile as the microbiome. For this study, the urinary microbiome was determined in mid-stream urine sample. All urine samples were collected prior to the start of the actual IVF or IVF-ICSI treatment [7].

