The predictive algorithm was developed in a pilot study comprising 42 women who were expected to start with either IVF or IVF-ICSI treatment and uses the percentages of the species *Lactobacillus*, *Staphylococcus* and *Escherichia coli* within the total microbiome of the sample. In the pilot study, the composition of the urinary microbiome prior to the start of the IVF or IVF-ICSI treatment was linked to the outcome of the ART treatment defined as ongoing pregnancy after one treatment cycle and pregnancy rates within 1 year after the initiation of the treatment. Cluster analysis and principal component analysis revealed that based on the microbiome composition it is possible to separate (by means of clustering) the women into two clusters: pregnant and non-pregnant women. After logistic regression, the bacterial species that dominated this prediction were identified and those were used to construct a predictive algorithm. In the pilot study, the test panel had a specificity of 96% and a sensitivity of 81%. Importantly, by adding the species *Bacillus RG4* the specificity improved up to 100%. The species found to be predictive has still to be confirmed in an independent, separate study. The crucial outcome of this predictive test is its specificity or better said, the prediction that the treatment will not result in pregnancy, since it could be used to select those women who should not be subjected to treatment because they will have a high chance not getting pregnant.

Hypotheses that might explain these finding is that the microbiome, acts as a sensor for the immunological tolerance that exist in secretory epithelia of a particular woman. Hence, it constitutes a proxy for endometrial receptivity which in turn depends on a similar immune response towards the developing embryo which is trying to implant. Another hypothesis is that the bacterial species included in the predictive algorithm possibly thrive the nutritional environment within epithelial secretions, which might be essential for initial survival of the embryo after transferral into the uterine cavity [8, 9].

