## Methods

### Study aim

With ReceptIVFity, we aim to validate the algorithm in a larger cohort, and to develop a predictive test suitable for the use in daily practice. In this cohort study, the following aims will be addressed:

Primary Objective:To assess the specificity and sensitivity of the urinary and vaginal microbiome composition for the prediction of embryo implantation failure of a consecutive IVF or IVF-ICSI procedure.

Secondary Objective:To assess the specificity and sensitivity of the urinary and vaginal microbiome composition for the prediction of the cumulative outcome of 1 year of subsequently performed IVF or IVF-ICSI procedures.

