### Strengths

The ReceptIVFity study will be the first cohort study in which the microbial composition will be used as predictor for IVF or IVF-ICSI outcome prior to the start of the treatment. As mentioned in the background section, several studies have found associations between the presence of microorganisms and reproductive outcomes, such as decreased implantation, pregnancy, ongoing pregnancy, and live birth rates. However, the clinical applicability of these findings has not yet been integrated into daily practice.

The ReceptIVFity cohort study consists of a large patient group/sample size and well-defined patients. A large sample is indicated, anticipating the fact patients can drop out for further treatment/follow up due to several reasons, such as poor response or total fertilisation failure. The included patients with embryo transfers will be used to investigate an association between microbial composition and IVF or IVF-ICSI outcome.

A prospective study design blinded for the test result, avoids bias to continue or not continue the treatment and allows for unbiased follow-up of the treatment outcomes.The 1 year follow-up is needed to examine the sustainability of the predicted outcome and will provide insight into the possibilities of becoming pregnant with subsequently performed IVF or IVF-ICSI procedures. Different techniques can be used to assess the microbiome and a high throughput technique is desirable for future application in daily practice. The prospective study validates the findings from the pilot study by the use of two different techniques. NGS that has become a gold standard for categorising bacteria or characterising microbial communities and the IS-pro technique which has the benefit of presenting results within 5 hours will be compared in this study. In addition, two sample sites (urine samples and vaginal swabs) will be compared with each other, both sites are easy to obtain by patients themselves. Developing a predictive test based on the urogenital microbiome composition will contribute to a personalised medicine approach in the future.

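### The plan promises to validate the pilot's urine algorithm and to report urinary accuracy, but the method it states builds and evaluates only a new vaginal algorithm

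*Protocol article*

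**What the plan says.** The Background describes an algorithm that already exists. In the pilot, "the urinary microbiome was determined in mid-stream urine sample", and the rule "uses the percentages of the species *Lactobacillus*, *Staphylococcus* and *Escherichia coli* within the total microbiome of the sample". In 42 women it reached a specificity of 96% and a sensitivity of 81%; adding *Bacillus RG4* raised specificity to 100%. The Background then adds: "The species found to be predictive has still to be confirmed in an independent, separate study".

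Under Study aim the article says "we aim to validate the algorithm in a larger cohort, and to develop a predictive test suitable for the use in daily practice". The primary objective is "To assess the specificity and sensitivity of the urinary and vaginal microbiome composition for the prediction of embryo implantation failure", and the secondary objective names the same two sites for the one-year outcome.

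The section Microbiome analysis and algorithm building says that, for the purpose of answering the study's questions, "an algorithm will be built based on the composition of the vaginal microbiome profile". The steps are exploration of pregnancy outcomes per community state type, then species content and diversity per phylum. Unfavourable and favourable profiles are defined for vaginal samples. The Statistical analysis section compares women by those profiles and adds no urine model.

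Under Strengths: "The prospective study validates the findings from the pilot study by the use of two different techniques". The same section says that urine and vaginal samples will be compared with each other.

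**The concern.** Validating an existing rule and building a new one are different analyses. Validation scores a fixed rule in new women. Development chooses predictors and cut-offs using the outcomes of the same women, so its apparent accuracy tends to be too high. The aim promises both, but the stated method covers only development, and at a different body site from the pilot.

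Two things are at stake. The pilot finding that motivates the cohort would be neither confirmed nor refuted by the analysis described. And one of the two sites in the primary objective would have no sensitivity or specificity to report, although urine is collected and profiled by both techniques.

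**Working it through.** **1. Promise against method.**

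| Element | Aim, objectives and Background | Algorithm section |
|---|---|---|
| Rule | Existing pilot algorithm, to be validated; also a practical test, to be developed | New algorithm, to be built |
| Sample | Pilot rule: urine. Objectives: urine and vagina | Vaginal profile |
| Predictors | Percentages of three taxa, optionally *Bacillus RG4* | Community state type, then species content and diversity |
| Classes | Sensitivity and specificity for both sites | Unfavourable and favourable, vaginal samples only |

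Sensitivity is defined as TP/(TP + FN) and specificity as TN/(TN + FP). All four counts need each woman to be classified by a rule. For vaginal samples the section supplies such a rule. For urine it supplies none, so the urinary counts do not exist. The later sentence about validating the formula directly follows the construction of the vaginal algorithm, and no other formula is in view there.

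The external cohort of 50 women is to validate the findings of this study. That tests the new rule.

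**2. How firm the pilot figures are.** The article gives percentages and n = 42, but no counts. Assuming all 42 women were evaluable, the only whole-number split that rounds to 81% and 96% is 13/16 and 25/26. Exact (Clopper-Pearson) 95% intervals:
- 13/16 = 81%: 54.4% to 96.0%
- 25/26 = 96%: 80.4% to 99.9%
- 26/26 = 100%: lower limit 0.025^(1/26) = 86.8%

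On this reading the rise to 100% is one woman.

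**3. What scoring the rule in the new cohort would give.** Inputs: 300 women (Abstract) and about 25% pregnant after a first cycle (Background), so 75 pregnant and 225 not. Half-width = 1.96 × √(p(1 − p)/n).
- 81% on 75: 1.96 × √(0.81 × 0.19/75) = 8.9 points; on 225: 5.1 points
- 96% on 225: 1.96 × √(0.96 × 0.04/225) = 2.6 points; on 75: 4.4 points

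If pregnancy is the positive class, the pair is ±9 and ±3. If failure is the positive class, as the primary objective and the algorithm section have it, the pair is ±5 and ±4. The article does not say which orientation the pilot figures use.

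These widths take all 300 women as evaluable. The article expects dropout before transfer but gives no figure. As an illustration, 200 women with a transfer and 25% pregnant (50 and 150) would give 6.3 to 10.9 points on the 81% and 3.1 to 5.4 points on the 96%.

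**The case against.** The article condenses a full protocol that is not shown. How a pilot rule is scored on urine data could stand there, so silence alone proves little. This is fair, and a reader should not infer that the pilot rule will never be scored. The point rests instead on an affirmative statement: the algorithm section assigns the study's questions to a vaginal algorithm. A urine analysis elsewhere would still leave the published text to be reconciled.

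The aim is dual, so building a new test is in scope. That stands, and it would be too much to call the whole cohort a second development study. Only the validation half and the urinary half lack a method.

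Urine is not unused: it is profiled by both techniques and compared with the swabs. That shows how the sites relate, not how well urine predicts.

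A reader might infer that community state types exclude *Staphylococcus* and *E. coli*. The text does not support this. The list for group IV is open, and a species-level step follows. Nor is the statement under Strengths plainly false, since it speaks of the pilot's findings and not of the fixed rule.

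Finally, the pilot used Sanger sequencing and the article prints no cut-offs or coefficients. Whether the rule carries over unchanged to NGS or IS-pro cannot be settled from the text. This stands and shapes the remedy.

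**Conclusion.** The point holds as a contradiction within the article. The aim names validation of the pilot algorithm and the primary objective names two sites. The stated method delivers a new rule at one site. Under it there is no urinary sensitivity or specificity and no test of the pilot rule. Because the primary objective is affected, this should be resolved before analysis.

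The contradiction depends on no figure. The figures show only that confirmation is needed and would be informative. They rest on three assumptions: all 42 pilot women evaluable, 25% pregnant, and all 300 women evaluable. Given these, precision is about ±5 to ±9 points on 81% and ±3 to ±4 on 96%, depending on the positive class, and worse after dropout.

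**What to change.** In the algorithm section, pre-specify two analyses.

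(a) *Validation.* Score the pilot rule, with and without *Bacillus RG4*, on the urine profiles of women with an embryo transfer. State failure to become pregnant as the positive class and express the pilot's own figures the same way. Report sensitivity and specificity with exact 95% intervals. If the rule is re-calibrated for NGS or IS-pro, label that version as updated and correct it for optimism, because it is then fitted to this cohort.

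(b) *Urine classification.* Define a urine-based classification and evaluate it in the same way as the vaginal one. Label the vaginal rule, based on community state types and species, as development.

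If the pilot rule cannot be transferred to the new techniques, reword the Discussion part of the Abstract, the Study aim and the Strengths section so that they no longer claim to validate the pilot algorithm.

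The cost is extra analysis of samples and outcomes already planned. The downside is that a Sanger-based rule may transfer imperfectly, so a poor result could reflect the change of technique as well as the rule itself.

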**Methods:**

In a prospective study, 300 women of reproductive age and with an indication for in-vitro Fertilization (IVF) with or without Intra Cytoplasmic Sperm Injection (ICSI) treatment will be included. Prior to the IVF or IVF-ICSI treatment, these women provided a midstream urine sample and a vaginal swab. The composition of the urinary and vaginal microbiome will be analysed with both Next Generation Sequencing and the IS-pro technique. The endpoints of the study are pregnancy achieved after fresh embryo transfer (ET) and within the subsequent year after inclusion. External validation of the findings will take place in an additional cohort of 50 women with an IVF or IVF-ICSI indication.

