**Discussion:**

In the proposed study, the predictive accuracy of the composition of the urinary and vaginal microbiome for IVF or IVF-ICSI outcome will be only validated for fresh ET. Follow-up has to show whether the predictive accuracy will be similar during the consecutive frozen ET’s as part of the IVF or IVF-ICSI treatment or for subsequent stimulated or natural cycles. In addition, external validation will take place in another cohort and hospital. Predictive knowledge of the microbiome profile may enable couples to make a more substantiated decision on whether to continue treatment or not. Hence, the unnecessary physical and emotional burden of a failed IVF or IVF-ICSI treatment can be avoided.

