### Statistical analysis

Statistical analyses of the clinical data will be performed by using SPSS statistics version 24 (IBM corp, Amonk, NY, USA). We will examine two different prediction models. In the prediction model for failure to become pregnant, the primary outcome will be defined as ‘not pregnant’ after the first fresh ET during IVF or IVF-ICSI treatment. In the prediction model for success to become pregnant, the primary outcome will be defined as ‘pregnant’. Normality of data will be determined by using the Shapiro-Wilks normality test. Continuous, normally distributed variables will be presented as mean with standard deviation, and variables with a skewed distribution as median with the range. Categorical variables will be presented as count and proportions.

Differences between the groups of women who will become pregnant and those who will not will be compared using Chi-square test or Fisher’s exact test for the categorical data, as appropriate. The Independent Samples t-test and Mann-Whitney U test will be used for continuous data. Two-sided *P* values less than 0.05 will be considered statistically significant. Applying the same method, differences between women with a favourable microbiome profile and those with an unfavourable profile will be compared.

Multivariate analysis will be performed using logistic regression with a selection of covariates that are known predictors for pregnancy outcome; age, duration of infertility and body mass index (BMI).

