## Discussion

In the ReceptIVFity cohort study, the specificity and sensitivity of the urogenital microbiome composition for the prediction of IVF or IVF-ICSI outcome will be determined in a cohort of women of reproductive age who will be expected to undergo their first IVF or IVF-ICSI cycle on short term. ReceptIVFity will investigate the role of a broad range of bacterial species and the influence of other clinical parameters in the success rate of IVF or an IVF-ICSI treatment. Insights in the microbial profile and their impact on the success rate may allow for a new strategy to decide whether to continue with treatment or not. The ultimate goal will be to develop a predictive algorithm that enables identification of the group of women with a low chance to become pregnant prior to the start of the IVF or IVF-ICSI treatment. Women with a low a priori chance to become pregnant might prefer to avoid the unnecessary physical and emotional burden of a IVF or IVF-ICSI treatment with a high change of failure.

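### The prediction rule is built from the pregnancy outcomes and its primary sensitivity and specificity come from the same women, so they are apparent values that will be too high; the external cohort of 50 is an unbiased but imprecise check

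*Protocol article*

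**What the plan says.** Under *Microbiome analysis and algorithm building*, the order of work is:

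- Building step one uses the outcome: "First, the algorithm will be built by exploration of the pregnancy outcomes per CST".
- Building step two widens the search: "In a subsequent step, the data will be analysed for species content and microbial diversity per phylum".
- Then: "The formula will be validated for prediction of failure to become pregnant after (the first) fresh embryo transfer". The formulas for sensitivity and specificity follow. That sentence does not name the women in whom validation takes place.

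Other sections supply the cohort. The main Discussion says of ReceptIVFity that "the specificity and sensitivity of the urogenital microbiome composition for the prediction of IVF or IVF-ICSI outcome will be determined in a cohort". The Abstract's Discussion presents validation for fresh transfer and then adds: "In addition, external validation will take place in another cohort and hospital". *Study aim* gives the one cohort two jobs, validating the algorithm and developing a test for daily practice, and makes sensitivity and specificity the primary objective.

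The main cohort is "300 women of reproductive age and with an indication for in-vitro Fertilization (IVF"). The independent data are described as: "External validation of the findings will take place in an additional cohort of 50 women with an IVF or IVF-ICSI indication".

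Under *Statistical analysis*, with a two-sided 0.05 level, "differences between women with a favourable microbiome profile and those with an unfavourable profile will be compared". The variables to be compared are not listed.

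**The concern.** A rule chosen because it separates pregnant from non-pregnant women in one dataset fits the chance features of that dataset as well as any real signal. Its accuracy in those women is, on average, better than it will be in new women. The article's sequence leads to exactly this figure as the primary result.

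The pilot does not avoid the problem. According to *Background*, the pilot rule used the percentages of three taxa in urine. The rule described now is built afresh on the vaginal profile, so for this rule the 300 women are development data.

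The stakes are high because of the intended use: helping couples decide whether to go on with treatment. *Background* calls specificity the crucial property. The predicted event is failure to become pregnant, so specificity is the share of women who do become pregnant whom the rule leaves unflagged. An overstated specificity hides women who would have conceived but were given an unfavourable profile.

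**Working it through.** The article states no precision or power target for either the 300 or the 50, so there is no sample-size figure to reproduce.

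**1. Which women supply the primary figures?** The validation sentence is silent. The main Discussion places sensitivity and specificity in the ReceptIVFity cohort, and the Abstract makes the external cohort an addition. Taken together, the natural reading is that rule and primary accuracy come from the same women. This is an inference from several sections, not a statement in one.

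**2. Direction and possible size of the optimism.** Assumed for illustration: 300 women, 25% pregnant, no true association; five CSTs plus K noise species with three cut-offs each; the best combination of two rules by sensitivity + specificity − 1 (Youden index, J); 600 runs per setting. With no association, a rule that flags a share f of women has true sensitivity f and true specificity 1 − f. Since f = 0.75 × sens + 0.25 × (1 − spec), the overstatement of specificity is 0.75 × J and that of sensitivity 0.25 × J.

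| K | apparent sens | apparent spec | J (true value 0) | spec too high by | sens too high by |
|---|---|---|---|---|---|
| 5 | 0.44 | 0.69 | 0.14 | 10 points | 3 points |
| 10 | 0.45 | 0.71 | 0.16 | 12 points | 4 points |
| 20 | 0.48 | 0.71 | 0.19 | 14 points | 5 points |
| 40 | 0.49 | 0.72 | 0.21 | 16 points | 5 points |

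With 195 women (an assumed 35% loss before transfer), J was 0.17 to 0.26. The sizes belong to this assumed search; the upward direction does not depend on it.

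**3. What the external cohort can show.** Inputs: 50 women (Abstract, Methods) and a first-attempt pregnancy rate of about 25% (*Background*). Pregnancies: 50 × 0.25 = 12.5, taken as 12, leaving 38 not pregnant.

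Exact (Clopper-Pearson) 95% limits:

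- Specificity 12/12: lower limit 0.025^(1/12) = 0.735, so 74% to 100%.
- Specificity 11/12: lower limit 62%.
- Sensitivity 31/38, close to the pilot's 81%: 66% to 92%.
- If 35% are lost before transfer (assumed), about 8 pregnancies: 8/8 gives 63% to 100%.
- At an assumed 40% pregnancy rate, 20 pregnancies: 19/20 gives 75% to 100%.

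Ability to see a fall from the pilot's 96%, by an exact one-sided test at 0.025: with 12 pregnancies the test rejects at 9 or fewer correct, since P(X ≤ 9) = 0.011 at 96% while P(X ≤ 10) = 0.081. The chance of that result is:

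| true specificity | 85% | 75% | 70% | 60% | 50% |
|---|---|---|---|---|---|
| power | 26% | 61% | 75% | 92% | 98% |

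At a true 85%, power is 11% with 8 pregnancies and 35% with 20.

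**The case against.** The strongest defence is that a journal article condenses a fuller plan. Resampling, optimism correction and a date for locking the formula could all stand in the unseen protocol or SAP, and the validation sentence names no cohort. That stands as a caution: one may not conclude that no internal validation exists. It does not remove the point, which rests on the sequence the article does state and on where it places the primary measures.

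Three stronger readings are tempting and are not supported:

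- *The profile is significance-tested against the outcome that defined it.* The comparison of favourable with unfavourable profiles names no variable and sits in a section on clinical data. It may concern age, BMI or duration of infertility, to which this objection does not apply. Only a test of pregnancy by profile in the building data would be affected.
- *The false-positive rate or the optimism can be quoted as a number.* Under three assumed search rules with 5, 10 and 20 candidates and no true effect, P<0.05 for pregnancy by profile occurred in 11/20/37%, 18/46/79% and 56/80/97% of datasets. A range of 11% to 97% shows that the size is driven by assumptions.
- *The external cohort is worthless or is not validation.* It comes from another clinic, in Germany, with inclusion through 2018, after main recruitment was due to end in March 2016. With a locked rule it is unbiased. Its weakness is precision, and it would very probably expose a specificity of 50% or 60%. Whether to call it exploratory is a matter of preference.

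**Conclusion.** The point holds in this form: followed as written, the plan reports apparent sensitivity and specificity as its primary result, and these will on average be too high. The direction is secure once rule and accuracy come from the same women, which is the natural reading of the sections together. The size is not established, because the article does not fix the search; the 10 to 16 points for specificity are an illustration only.

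The external cohort can correct the bias in principle but not precisely. Its limits rest on the 25% rate, which is per first attempt rather than per transfer, and on 50 evaluable women; the range of 8 to 20 pregnancies does not change the conclusion. It can reveal a gross failure, has 61% power at a true specificity of 75% and 26% at 85%, and cannot confirm a specificity near 96%. The article sets no threshold for an acceptable specificity, so no claim is made about which shortfall would matter clinically.

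**What to change.** In *Microbiome analysis and algorithm building*:

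1. Name the women who supply the primary sensitivity and specificity.
2. Write the building procedure (CST step, species selection, cut-offs) as an algorithm that can be rerun without judgement.
3. Repeat the whole of it inside cross-validation, for example leaving out one of the eight centres at a time if centre sizes allow, or inside a bootstrap that corrects for optimism. Report the corrected sensitivity and specificity as primary, with the apparent values beside them and labelled as such.
4. Lock the formula before the external outcomes are opened, and report external sensitivity and specificity with exact confidence intervals.

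In *Statistical analysis*: if pregnancy is compared between profile groups in the building data, present it descriptively without a P value. Comparisons of age, BMI and other characteristics may stay.

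Cost: no new patients or samples. The work lies in turning an exploratory search into a fixed algorithm and programming the resampling. Reported accuracy will be lower, with wider intervals.
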